### Secondary outcomes

Secondary outcomes will assess changes in related clinical domains, including depressive symptoms, anxiety symptoms, suicidality, sleep quality, global clinical status, rumination, and health-related quality of life.

Depressive symptoms will be assessed using the Beck Depression Inventory-II (BDI-II). Anxiety symptoms will be assessed using the Hamilton Anxiety Rating Scale (HAMA) and the Screen for Child Anxiety Related Emotional Disorders (SCARED) [29]. Suicidality will be assessed using the Columbia-Suicide Severity Rating Scale (C-SSRS) [30]. Sleep quality will be assessed using the Pittsburgh Sleep Quality Index (PSQI). Global clinical status will be assessed using the Clinical Global Impression-Severity (CGI-S) and the Clinical Global Impression-Improvement (CGI-I) [31]. Rumination will be assessed using the Ruminative Responses Scale (RRS), and health-related quality of life will be assessed using the Pediatric Quality of Life Inventory 4.0 (PedsQL 4.0).

For secondary outcomes, changes from baseline will be evaluated where applicable. CGI-I will be assessed at post-baseline visits to evaluate overall clinical improvement relative to baseline. Secondary outcomes will be assessed at baseline, during treatment, at the end of treatment, and during follow-up up to 6 months, as specified in the assessment schedule. The C-SSRS will also be administered throughout the study to support ongoing safety monitoring of suicidal ideation and suicidal behaviors.

### Exploratory outcomes

Exploratory outcomes will include MRI-derived functional connectivity, cognitive performance, and multimodal neurophysiological and behavioral measures. MRI-derived functional connectivity will be analyzed using seed-based or whole-brain approaches to examine modulation of depression-relevant circuits. Cognitive performance will be assessed using THINC-it [32]. Multimodal exploratory biomarkers will be assessed, including electroencephalography (EEG), eye tracking, functional near-infrared spectroscopy (fNIRS), facial expression features, and acoustic features.

These exploratory measures will be collected according to the assessment schedule at baseline, at the end of treatment, and during follow-up where applicable. They will be used to characterize potential cognitive, neurophysiological, behavioral, and affective changes associated with treatment and are not designated as primary or secondary outcomes. The schedule of outcome assessments is shown in Table 1.

**Table 1 pone.0355676.t001:** Study of efficacy outcome measures.

Outcomes	Measure	Time points
Primary Outcomes	Recruitment Feasibility	At 2 years
	Intervention adherence	At 4 weeks
	Retention Rate	At 24 weeks
	Adverse events and serious adverse events recorded	At 2, 4, 8, 16 and 24 weeks
	CDRS-R	Response at the end of treatment (Week 4) (defined as≥50% reduction in CDRS-R from baseline) or Remission at the end of treatment (Week 4) (defined as CDRS-R ≤ 28)
Secondary Outcomes	BDI-II	At 2, 4, 8, 16 and 24 weeks
	HAMA	At 2, 4, 8, 16 and 24 weeks
	SCARED	At 2, 4, 8, 16 and 24 weeks
	C-SSRS	At 2, 4, 8, 16 and 24 weeks
	PSQI	At 2, 4, 8, 16 and 24 weeks
	PedsQL 4.0	At 2, 4, 8, 16 and 24 weeks
	CGI-I	At 2, 4, 8, 16 and 24 weeks
	CGI-S	At 2, 4, 8, 16 and 24 weeks
	RRS	At 2, 4, 8, 16 and 24 weeks
Exploratory Outcomes	MRI	At 4, 8, 16 and 24 weeks
	THINC-It	At 4, 8, 16 and 24 weeks
	EEG	At 4, 8, 16 and 24 weeks
	fNIRS	At 4, 8, 16 and 24 weeks
	Eye tracking	At 4, 8, 16 and 24 weeks
	Facial expressions	At 4, 8, 16 and 24 weeks
	Acoustic features	At 4, 8, 16 and 24 weeks

CDRS-R, Children’s Depression Rating Scale-Revised; HAMA, Hamilton Anxiety Rating Scale; BDI-II, Beck Depression Inventory-II; SCARED, Screen for Child Anxiety Related Emotional Disorders; C-SSRS, Columbia-Suicide Severity Rating Scale; CGI-I, Clinical Global Impression-Improvement Scale; CGI-S, Clinical Global Impression-Severity Scale; RRS, Rumination on Responses Scale.

### Data collection and management

Data will be collected using standardized questionnaires, clinical assessments, neuroimaging measures, and multimodal physiological or behavioral assessments, as applicable. All study instruments and outcome measures will be selected on the basis of established reliability and validity. Completed questionnaires and assessment records will be stored on a secure cloud-based platform, and results of clinical examinations and imaging assessments will be uploaded as formal reports. Data entry will be performed by authorized study personnel using access-controlled accounts to ensure data security, confidentiality, and integrity. Quality control procedures will include double data entry, routine data checks, and periodic verification to ensure accuracy and completeness. All data management processes will be documented and conducted in accordance with applicable regulations and institutional policies governing clinical trial data handling.

### Safety considerations and adverse events

Internationally accepted definitions of adverse events (AEs) and serious adverse events (SAEs) will be applied. An AE will be defined as any unfavorable and unintended medical occurrence in a participant receiving transcranial magnetic stimulation, regardless of whether it is considered related to the intervention. An SAE will be defined as any event that results in death, is life-threatening, requires hospitalization or prolongation of hospitalization, results in persistent or significant disability or incapacity, or involves a congenital anomaly or birth defect. After each treatment session, participants will be systematically asked about any adverse reactions or other medical events experienced, and all AEs and SAEs will be documented and managed in accordance with the trial’s safety procedures.

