### Exclusion criteria

Participants meeting any of the following criteria will be excluded from this study.

Psychiatric comorbidities other than anxiety disorders;Depression with psychotic symptoms;Young Mania Rating Scale (YMRS) score >13;A history of neurological disorders (e.g., epilepsy, brain injury) or severe somatic diseases (e.g., thyroid disorders, lupus, diabetes, pulmonary, hepatic, or renal impairment, major trauma);Patients currently using anticonvulsants or high-dose benzodiazepines;A history of electroconvulsive therapy (ECT), transcranial magnetic stimulation (TMS), transcranial direct current stimulation (tDCS), transcranial alternating current stimulation (tACS), or other neuromodulation treatments;A history of alcohol or substance abuse or dependence;Women who are pregnant or breastfeeding;Current high suicide risk;Potential complicating factors related to transcranial magnetic stimulation, such as scalp conditions or perforations that may affect magnetic field delivery;Contraindications to MRI.

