## Outcomes

### Primary outcomes

The primary outcomes of this pilot trial are feasibility, safety, and preliminary clinical efficacy.

Feasibility will be evaluated using three indicators: recruitment feasibility, intervention adherence, and retention at the 6-month follow-up. Recruitment feasibility will be defined as the number of participants successfully enrolled during the 2-year recruitment period. Intervention adherence will be defined as the proportion of participants who complete all 20 planned treatment sessions. Retention will be defined as the proportion of enrolled participants who complete the 6-month follow-up assessment.

Safety will be evaluated by recording the incidence of adverse events and serious adverse events throughout the treatment and follow-up periods. The type, severity, outcome, and relationship of each adverse event to the intervention will be documented.

Preliminary clinical efficacy will be evaluated using the CDRS-R. CDRS-R total score will be assessed at baseline, at the end of treatment (week 4), and at follow-up weeks 8, 16, and 24. Response will be defined as a reduction of at least 50% in the CDRS-R total score from baseline, and remission will be defined as a CDRS-R total score of 28 or lower [28]. Response and remission will be determined at post-baseline assessments, using the baseline CDRS-R total score as the reference.

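### The five-item SAE list leaves a seizure or suicide attempt without admission as non-serious, and C-SSRS findings do not enter the safety summaries

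*Protocol article*

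**What the plan says.** All references are to the Protocol article.

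- **Definitions** (Safety considerations and adverse events). The section opens with "Internationally accepted definitions of adverse events (AEs) and serious adverse events (SAEs) will be applied". It then gives the trial's own wording: "An SAE will be defined as any event that results in death, is life-threatening, requires hospitalization or prolongation of hospitalization", and the list closes with "results in persistent or significant disability or incapacity, or involves a congenital anomaly or birth defect". No general clause follows, and no specific event is named. An adverse event is "any unfavorable and unintended medical occurrence in a participant receiving transcranial magnetic stimulation, regardless of whether it is considered related to the intervention".
- **Primary safety outcome** (Primary outcomes). "Safety will be evaluated by recording the incidence of adverse events and serious adverse events throughout the treatment and follow-up periods". Type, severity, outcome and relationship are recorded for each event.
- **Summary measures** (Analysis of primary outcomes; Safety analysis). For AEs and for SAEs, the incidence is the number and share of participants in each arm with one or more events. Event counts and severity are described as well. Safety analysis adds a breakdown by type and a chi-square or Fisher comparison between arms.
- **C-SSRS** (Secondary outcomes; Analysis of secondary outcomes; Table 1). It is a secondary outcome, analysed alongside the BDI-II, HAMA and other scales. The article adds: "The C-SSRS will also be administered throughout the study to support ongoing safety monitoring of suicidal ideation and suicidal behaviors". Table 1 schedules both the C-SSRS and AE/SAE recording at weeks 2, 4, 8, 16 and 24.

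**The concern.** Seizure and suicidal behaviour are harms that a reader of this trial will look for first. The article itself treats them as important: it excludes a history of epilepsy and "Current high suicide risk", and its introduction names suicidal behaviour as a feature of severe adolescent depression.

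The SAE list works only through consequences such as death, admission or disability. Two participants with the same seizure could be classed differently because one was admitted and the other was not. The instrument that detects suicidal behaviour reports into a different part of the analysis. At stake is how clearly the published safety results separate these events from minor ones. AE and SAE incidence is a primary outcome and a main product of the pilot for the next trial.

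**Working it through.** The article derives no figure on this point, so the check is a reading of the sections against each other, followed by one small calculation.

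**1. Is the event an SAE?** Take a self-limiting seizure, or a suicide attempt, that is not life-threatening and leads to no admission and no lasting disability. Against the list: death, no; life-threatening, no; admission or prolonged stay, no; disability, no; congenital anomaly, not applicable. No clause remains that could catch it. As written, it is not an SAE. An otherwise identical event followed by admission is one.

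**2. Is it an AE?** The AE definition has no threshold for seriousness or relatedness, so the seizure qualifies. A suicide attempt would ordinarily be recorded as an AE too, although the text does not say so.

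**3. Where does it appear in the primary safety summaries?**
- In the SAE proportion: nowhere.
- In the any-AE proportion: as one participant with an event. The introduction names scalp discomfort and headache as the most common effects in adults. If *k* of 15 participants already have an AE and the affected participant is one of them through a headache, the proportion stays at *k*/15. If not, it moves to (*k* + 1)/15, exactly as it would for a headache.
- In the tabulation by type and severity: as a line among others. Neither seizure nor suicidal behaviour is a prespecified row. Severity grading is also a separate matter from seriousness.

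**4. Does the C-SSRS supply what is missing?** It is given throughout the study and supports monitoring. In the analysis it appears only under secondary outcomes. Analysis of primary outcomes and Safety analysis do not mention it, and the article does not say how a positive finding enters the AE or SAE count. Systematic questioning about events is described only after treatment sessions. During follow-up, AE recording and the C-SSRS fall at the same visits, with no stated link between them.

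**5. Size.** Inputs: 15 participants per arm (Sample size), assuming that all receive at least one session and so enter the safety set.
- SAE incidence with the event classed as non-serious, and no other SAE: 0/15 = 0%.
- SAE incidence with the same event classed as serious: 1/15 = 6.7%.

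Any single event would move the figure by this much. What matters is that the difference can turn on an admission decision rather than on what happened to the participant.

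**The case against.** The strongest reply is that nothing is lost. The primary safety outcome covers every AE, with type and severity, so a seizure without admission is recorded and tabulated. The lead-in invokes internationally accepted definitions, the section refers to the trial's own safety procedures, and the full protocol and analysis plan are said to be public. Rules for events of special interest are often left to such documents.

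Much of this stands, and it limits the point:

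- A reader might infer that the primary safety outcome misses these events. It does not. The risk is that they are under-classified and diluted.
- A reader might infer that suicidality is not treated as a safety matter. The article says that the C-SSRS supports safety monitoring.
- A reader might infer from the exclusion of high suicide risk that the C-SSRS has little room to improve. The article gives no threshold and no baseline distribution, and entrants are in a current depressive episode with CDRS-R of at least 40. Nor does it commit the C-SSRS to a mean change: change from baseline applies only where suitable, and ordinal or categorical outcomes have their own methods.
- A reader might infer from "any unfavorable and unintended medical occurrence in a participant receiving transcranial magnetic stimulation" that sham participants fall outside the AE definition. The safety set includes anyone with at least one active or sham session, and recording runs through follow-up, which largely settles this.
- SAE status is not the only trigger for discontinuation or for committee recommendations. Both sections name others, so the main effect is on classification and reporting.

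What the reply does not remove is the list itself. It is stated wording, not a detail left out, and it reads as complete. The lead-in neither cites nor reproduces the definitions that it invokes, so the reader cannot tell which governs.

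**Conclusion.** The point holds as a moderate gap in classification and reporting. As written, a seizure or suicide attempt that meets none of the five criteria is a non-serious AE. It has no distinct place in the participant-level incidence figures, and C-SSRS findings have no stated route into the safety summaries. An arm could be reported with 0/15 SAEs when such an event occurred in it, against 1/15 (6.7%) had the same event led to admission.

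This rests on two assumptions: that the printed list is the operative definition, and that the full protocol does not already add a residual clause or named events. If it does, the article's wording only needs to be brought into line.

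The documents do not support going further and requiring every interrupted or aborted attempt to be an SAE. That is a reporting choice; no section demands it, and a named row makes such events visible without it.

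**What to change.** For counting and reporting only, with no change to clinical management:

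1. Reconcile the SAE list with its lead-in by adding a clause for other medically important events, and say which definition governs.
2. In the primary safety table, report by arm, in the safety set and through week 24, two kinds of named event whatever the admission status: seizures, and treatment-emergent suicidal ideation and behaviour on the C-SSRS relative to baseline.
3. State how a positive C-SSRS finding enters the AE and SAE records, so that the two sources can be reconciled at each visit.

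The C-SSRS is already collected at baseline and at weeks 2, 4, 8, 16 and 24, so the cost is protocol wording and one table. The reported serious-event count may rise, and the report should say that this follows from the definition.

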## Methods

### Study design and setting

This investigator-initiated, single-center pilot trial is designed to evaluate the feasibility, safety and preliminary clinical efficacy of rs-fcMRI-guided rTMS in adolescents with MDD. Participants will be randomly assigned to one of three parallel arms: conventional left dorsolateral prefrontal cortex (DLPFC)-targeted rTMS, rs-fcMRI-guided rTMS targeting an individualized DLPFC site defined by DLPFC-sgACC functional connectivity, or sham rTMS.

The study adopts a randomized, double-blind, three-arm, sham-controlled, parallel-group pilot design and will be conducted at the First Affiliated Hospital of Chongqing Medical University (Chongqing, China) from September 2025 to September 2027. A total of 45 adolescents will be enrolled, with 15 participants allocated to each group in a 1:1:1 ratio. Participant recruitment commenced in September 2025 and is expected to be completed by December 2026. Recruitment will be monitored throughout the study to assess enrolment feasibility and ensure timely participant accrual. At the time of manuscript submission, the study is ongoing, and no study results have been generated. Data collection is expected to be completed by June 2027, and study results are anticipated to be available by September 2027.

The study protocol was approved by the Ethics Committee of the First Affiliated Hospital of Chongqing Medical University (Ethical Approval No. 2025-533-01) and registered at ClinicalTrials.gov (NCT07185438).

This pilot trial consists of a 7-day screening period, a 4-week intervention phase, and follow-up assessments up to 6 months. After eligibility has been confirmed, participants and their legal guardians will provide written informed consent, and participants will undergo baseline assessments, including MRI. Participants will then be randomly assigned to one of three groups to receive a 4-week course of active or sham rTMS. Follow-up assessments will be performed at weeks 8, 16, and 24 to evaluate clinical outcomes and safety over time. Cognitive and multimodal measures, including EEG, fNIRS, eye-tracking measures, facial expression features, and acoustic features, will also be collected at baseline, at the end of treatment, and during follow-up as exploratory measures.

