### rTMS delivery and general procedures

rTMS will be delivered using the Black Dolphin TMS robotic system (Spirit Dolphin, SLD-YXRJ-V1.0, Solide Company, Xi’an, China) equipped with a figure-of-eight coil. Individualized neuronavigation will be supported by a personalized three-dimensional facial tracking model generated from each participant’s MRI data, allowing the robotic arm to position the coil accurately over the predefined stimulation target across treatment sessions.

Before the first treatment session, the resting motor threshold (RMT) will be determined for each participant. The RMT is defined as the minimum stimulation intensity required to elicit motor-evoked potentials in at least 5 of 10 trials. Participants in all three study arms will receive a 4-week course of active or sham stimulation consisting of 20 weekday sessions, with identical treatment frequency and procedural workflow across groups.

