### Stimulation parameters

For both active treatment groups, stimulation parameters will be identical: frequency 10 Hz, intensity 120% of the individual RMT (reducible to 110% of RMT during week 1 if not tolerated), 2400 pulses per session, and a session duration of approximately 40 minutes. Treatment will be administered once daily on weekdays for a total of 20 sessions over 4 weeks.

In the sham group, participants will undergo the same treatment schedule and procedural workflow as those in the active groups, but stimulation will be delivered with a sham coil that reproduces the acoustic and tactile sensations of active rTMS while minimizing meaningful magnetic field penetration.

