#### Analysis of primary outcomes.

Primary outcomes will be analyzed descriptively in accordance with the pilot nature of the trial. Feasibility outcomes will include recruitment feasibility, intervention adherence, and retention at the 6-month follow-up. Recruitment feasibility will be summarized as the number of participants enrolled during the recruitment period. Intervention adherence and retention will be summarized as frequencies and proportions, with corresponding 95% confidence intervals calculated where appropriate.

Safety outcomes will be analyzed in the safety analysis set, defined as all participants who receive at least one session of active or sham stimulation. The incidence of adverse events and serious adverse events will be summarized by treatment group as the number and proportion of participants experiencing at least one event. Event counts, severity, outcomes, and relationship to the intervention will also be summarized descriptively.

Preliminary clinical efficacy will be evaluated in terms of response and remission based on CDRS-R total scores. Response and remission rates will be summarized descriptively by treatment group at the end of treatment and at each follow-up assessment, with 95% confidence intervals. Exploratory between-group comparisons may be conducted using logistic regression models at individual post-baseline time points or generalized estimating equations for repeated binary outcomes across follow-up, as appropriate. Effect estimates will be presented as odds ratios with 95% confidence intervals.

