### Safety analysis

Safety outcomes will be summarized descriptively by treatment group, including the type, frequency, severity, and incidence of adverse events and serious adverse events. Between-group comparisons will be conducted using the chi-square test or Fisher’s exact test, as appropriate. Tolerability-related indicators, including treatment interruption, dose reduction, or discontinuation, will also be summarized descriptively.

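### Adverse-event incidence pools 4 weeks of treatment with 20 weeks of follow-up, which can dilute the between-arm safety comparison

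*Protocol article*

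**What the plan says.** The inquiry rule is in the Protocol article, Safety considerations and adverse events: "After each treatment session, participants will be systematically asked about any adverse reactions or other medical events experienced". Stimulation parameters fixes how many sessions there are: "Treatment will be administered once daily on weekdays for a total of 20 sessions over 4 weeks". The same section on adverse events counts an event whether or not it is judged related to the intervention.

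After treatment, Study design and setting says: "Follow-up assessments will be performed at weeks 8, 16, and 24 to evaluate clinical outcomes and safety over time". Table 1 has a row for "Adverse events and serious adverse events recorded" at weeks 2, 4, 8, 16 and 24, so three scheduled points fall after week 4.

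The outcome covers both periods. Under Primary outcomes: "Safety will be evaluated by recording the incidence of adverse events and serious adverse events throughout the treatment and follow-up periods". Under Analysis of primary outcomes, incidence is "summarized by treatment group as the number and proportion of participants experiencing at least one event", with counts, severity, outcome and relationship described alongside. Safety analysis adds the test: "Between-group comparisons will be conducted using the chi-square test or" Fisher's exact test. None of these places splits the measure by period or relates it to sessions attended.

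**The concern.** The proportion with at least one event is cumulative. Once a participant has any event at any time up to week 24, later or earlier events no longer matter to it. The arms differ in what is done to participants only in weeks 0 to 4. The following 20 weeks add headaches, infections and other ordinary events to every arm. Each sham participant with such an event moves into the same category as an active participant who had a treatment-related one, and the difference between arms narrows.

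The problem reaches the estimate as well as the test. The article puts estimation first, and the estimated risk difference itself is diluted. The Discussion says that feasibility and safety outcomes will help decide whether the protocol needs changing before a larger trial, so an understated tolerability difference would carry forward.

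A second, smaller point is that the safety set requires only one session, and data collection stops at withdrawal. A participant who attends fewer sessions is asked fewer times and has fewer chances to be counted.

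**Working it through.** **Inputs from the article.** 20 sessions in 4 weeks; three scheduled recording points in weeks 4 to 24; 15 participants per arm. The article gives no adverse-event rate and no safety power figure, so there is no stated figure to reproduce. All event rates below are assumptions.

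**Intensity of inquiry.** Treatment: 20/4 = 5 per week. Follow-up: 3/20 = 0.15 per week. The ratio is about 33.

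**Model.** Let q be the chance of reporting an event at one session, independent across sessions. Then P(at least one in treatment) = 1 − (1 − q)^20. Let f be the chance of reporting an event at one follow-up visit, equal in all arms and independent of treatment-period events. Then F = 1 − (1 − f)^3. The pooled proportion is 1 − (1 − P)(1 − F), so the pooled difference equals the treatment-period difference times (1 − F).

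**Treatment period alone, 2% against 10% per session.**
- Sham: 1 − 0.98^20 = 33.2%
- Active: 1 − 0.90^20 = 87.8%
- Difference: 54.6 points

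**Pooled to week 24.** Power is for the exact two-sided Fisher test at 0.05, 15 against 15.

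| f per visit | F | 1 − F | Difference, 2% vs 10% | Power | Difference, 2% vs 5% | Power |
|---|---|---|---|---|---|---|
| treatment period only | – | – | 54.6 | 80% | 30.9 | 24% |
| 5% | 14.3% | 0.857 | 46.8 | 67% | 26.5 | 17% |
| 15% | 38.6% | 0.614 | 33.5 | 44% | 19.0 | 10% |
| 30% | 65.7% | 0.343 | 18.7 | 14% | 10.6 | 5% |

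**Attendance.** With the same risk per session in everyone, the proportion with at least one event still depends on the number of sessions attended.

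| q | 5 sessions | 10 | 15 | 20 |
|---|---|---|---|---|
| 2% | 9.6% | 18.3% | 26.1% | 33.2% |
| 5% | 22.6% | 40.1% | 53.7% | 64.2% |
| 10% | 41.0% | 65.1% | 79.4% | 87.8% |

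**Ceiling.** At 10% against 20% per session, treatment alone gives 87.8% against 98.8%, a difference of 11.0 points with Fisher power of 2%. Splitting the periods does not cure this; it is the reason to show event counts as well.

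**Capture in follow-up.** The follow-up gaps are 4, 8 and 8 weeks. If a visit question reaches back w weeks, the share of follow-up covered is [min(w,4) + 2·min(w,8)]/20. This gives 15%, 30%, 60% and 100% for 1, 2, 4 and 8 weeks. The article states no look-back interval.

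**The case against.** The strongest reply is that participants with at least one event per arm, with Fisher's test, is a conventional safety summary. The article is a condensed account, and treatment and follow-up tables may well be in the analysis plan, which is not shown. P values are only supportive and the sample size is pragmatic, so loss of power is a weak complaint. Counts, type, severity and relationship are planned too. Asking after every session is good practice, and the schedule is the same in all arms ("with identical treatment frequency and procedural workflow across groups").

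Most of this stands. It limits the point to the summary that the article does fix: a primary outcome defined over both periods, reported as one proportion and tested between arms. Dilution of that proportion affects the estimate as well as the P value, and the planned counts are stated without a period or a session denominator.

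Three stronger readings are not supported:

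- **Safety will appear to improve over time simply because participants are asked less often.** A single cumulative proportion cannot fall and shows no trend, and the article describes no time-trend analysis of adverse events. An artificial decline would need events tabulated by period and visit questions that miss part of the interval. If the questions cover the full interval, capture is 100% and the artefact disappears. A real fall after stimulation ends is also plausible.
- **Attendance biases the comparison.** It does so only if attendance differs by arm. Adherence and discontinuation are both reported, so a difference should be visible.
- **Nearly everyone will have an event, so the arms cannot be separated.** That depends on high per-session rates that the documents do not give. At 2% against 10%, the treatment-period proportion separates the arms well.

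**Conclusion.** The point holds as a dilution problem in the stated safety measure. Under the assumed 2% and 10% per session, pooling removes about 8, 21 or 36 of 54.6 points (54.6 − 46.8, 54.6 − 33.5, 54.6 − 18.7), depending on how often background events are reported in follow-up. The loss is modest at 5% per visit and large at 30%.

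These figures assume independence between sessions and periods, full attendance and equal follow-up rates across arms. If the participants who report events in treatment are also those who report them later, the dilution is smaller. Few events captured in follow-up also means little dilution. The true size is therefore unknown. The change is still worth making because it is cheap and leaves the sample size untouched.

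**What to change.** In Analysis of primary outcomes and Safety analysis:

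1. Report adverse events separately for treatment (first session to week 4) and follow-up (weeks 4 to 24), and base the main between-arm safety comparison on the treatment period.
2. Keep the proportion with at least one event. Beside it, give event counts per session attended, with a 95% confidence interval that allows for clustering within participant.
3. State both inquiry schedules together, after each session and at the visits in Table 1, and say that the questions at weeks 8, 16 and 24 cover the whole interval since the last visit.
4. State that a difference in event frequency between treatment and follow-up will not be read as a change in safety, because ascertainment differs.

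Rates per person-week from the visit questions alone would not rescue a time comparison. The visit gaps are 2, 2, 4, 8 and 8 weeks. With 7-day recall, coverage would be 50%, 50%, 25%, 12.5% and 12.5%, so a constant true rate would still appear to fall fourfold.

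The cost is two adverse-event tables instead of one and a few sentences of wording. No extra visits or participants are needed. If the analysis plan already splits the periods, the article only needs to be aligned with it.
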